## Abstract

**Background:**

The risk of acquisition of antibiotic resistant-bacteria during or shortly after antibiotic therapy is still unclear and it is often confounded by scarce data on antibiotic usage.

Primary objective of the study is to compare rates of acquisition of methicillin-resistant *Staphylococcus aureus *and extended spectrum beta-lactamase-producing *Enterobacteriaceae *in hospitalised patients, after starting antibiotic therapy.

**Methods/Design:**

The study, running in three European hospitals, is a multicenter, prospective, longitudinal, observational cohort study funded from the European Community's Seventh Framework Programme [FP7/2007-2013] within the project 'Impact of Specific Antibiotic Therapies on the prevalence of hUman host ResistaNt bacteria' (acronym SATURN). Nasal and rectal screening for methicillin-resistant *Staphylococcus aureus *and extended spectrum beta-lactamase-producing *Enterobacteriaceae *will be obtained at hospital admission, discharge, at antibiotic start (t_0_, within one hour) and at the following intervals: day 3 (t_1_), 7 (t_2_), 15 (t_3_), and 30 (t_4_). Two nested case-control studies will be performed. The objective of the first study will be to define individual level of risk related to specific antibiotics. Patients acquiring methicillin-resistant *Staphylococcus aureus *and extended spectrum beta-lactamase-producing *Enterobacteriaceae *(cases) will be compared with patients not acquiring antibiotic-resistant strains after starting antibiotic therapy (controls; ratio 1:4). To define the impact of antibiotics on new acquisition of target antibiotic-resistant bacteria, a second nested case-control study will be done (ratio 1:4). Control group will be selected among patients not receiving antibiotics, admitted in the same ward on the day of the corresponding case, with negative cultures at admission. Epidemiological, clinical and microbiological data will be prospective collected.

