## Testing the hypothesis

All adult patients (> 18 years) starting intravenous and/or oral antibiotic treatments during hospitalisation will be included in the study. Written informed consent will be obtained by every patient before study inclusion. Exclusion criteria will be pregnancy and recent nose surgery. Patients starting antibiotic therapy *per os *and/or intravenously will be sampled at antibiotic start (t_0_, within one hour) and at the following intervals: day 3 (t_1_), 7 (t_2_), 15 (t_3_), 30 (t_4_) (Figure 1). Patients colonised with MRSA and/or extended-spectrum β-lactamase (ESBL)-producing gram-negative bacteria before starting antibiotic therapy (t_0 _sample) will be excluded from follow-up cultures and analysis. Patients will be followed during the hospitalisation and afterwards for a total of 30-day from the inclusion in the study. Screening will be performed in outpatient clinics after patients' discharge from the hospital, if possible.

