### Statistical analysis

The assessable population for each target organism will include all treated patients from whom baseline screening and at least one follow-up screening will be available. The incidence of colonisation will be defined by the number of new cases of colonisation for 1,000 days of antibiotic therapy. Only patients with a negative baseline (t_0_) will be included in the longitudinal analysis. The length of exposure to antibiotic therapy for patients newly colonised by ARB will be defined by the number of days between the inclusion in the study and the date of the first positive sample. The length of exposure to antibiotic therapy for patients not colonised will be defined by the number of days between the inclusion in the study and the date of antibiotic discontinuation. The colonisation pressure will be calculated for each center and defined as the average point of prevalence for antibiotic-resistant bacteria for all days until acquisition or discharge. Time-to-event analysis (in days) between the inclusion in the study and the acquisition of colonisation will be done using Kaplan-Meier curves and Cox proportional hazard regression modeling in which the number of days until acquisition will be the dependent variable. Two nested case-control studies will be performed:

#### Case control study 1

To define the impact of antibiotics on new acquisition of MRSA and ESBL-producing *Enterobacteriaceae*, a matched case-control study will be done (ratio 1:4). The control group will be selected among patients not receiving antibiotics, admitted in the same ward on the day of the corresponding case, with negative cultures at hospital admission. Matching criteria will include: age (± 5 years), sex, and total length of hospitalisation.

#### Case control study 2

To define individual level of risk related to specific antibiotics, patients acquiring MRSA and ESBL-producing *Enterobacteriaceae *will be compared with patients not acquiring ARB after starting antibiotic therapy (ratio 1:4). Previously known risk factors or clinically relevant significant variables from the univariate analysis will be considered for inclusion in multivariate logistic regression analysis. The Hosmer and Lemeshow goodness-of-fit test will be used to assess model fit.

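### In the treated-versus-untreated case-control study, acquisition is looked for more often and for longer in patients on antibiotics, so the comparison is biased, usually towards an antibiotic effect

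*Protocol article*

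**What the plan says.** **Who is swabbed, and when.** The abstract (Methods/Design) gives the general schedule: swabs "will be obtained at hospital admission, discharge, at antibiotic start (t_0_, within one hour) and at the following intervals: day 3", and so on up to day 30. In Testing the hypothesis, the cohort consists of adults "starting intravenous and/or oral antibiotic treatments during hospitalisation will be included in the study". The interval swabs belong to this cohort: those starting therapy by mouth "and/or intravenously will be sampled at antibiotic start (t_0_, within one hour) and at the following intervals: day 3 (t_1_), 7 (t_2_), 15 (t_3_), 30". Follow-up does not stop at discharge: "Patients will be followed during the hospitalisation and afterwards for a total of 30-day from the inclusion in the study". For the time after the patient has left, the section adds: "Screening will be performed in outpatient clinics after patients' discharge from the hospital, if possible".

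**Who is excluded at t0.** The same section removes patients already colonised at the t0 sample from follow-up cultures and from the analysis.

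**What study 1 compares.** In Statistical analysis, case control study 1 is done "To define the impact of antibiotics on new acquisition of MRSA and ESBL-producing" organisms. On the comparison group it says: "The control group will be selected among patients not receiving antibiotics, admitted in the same ward on the day of the corresponding case". The one culture condition that it sets for these controls is that they are patients "with negative cultures at hospital admission". Cases and controls are matched on age within five years, sex and total length of stay. (The abstract lists this comparison as the second nested study. The numbering of the Statistical analysis section is used here.)

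**The concern.** A patient who never starts an antibiotic has no t0, so days 3, 7, 15 and 30 are undefined for that patient. The only culture condition set for study 1 controls is a negative one at admission. A treated patient can therefore be found positive at up to four scheduled follow-up swabs plus discharge, over 30 days. An untreated patient can be found positive at one swab at most, at discharge.

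An acquisition found only after discharge, or found in hospital but missed or cleared by discharge, can make a case only of a treated patient. Matching on length of stay equalises time in hospital. It equalises neither the number of swabs nor the time after discharge.

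The question of study 1 is the effect of antibiotics on acquisition. Part of any association it reports would come from how hard acquisition was looked for. The Background cites a 1.8-fold MRSA risk with antibiotics, and an artefact of that order is possible.

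**Working it through.** The plan gives no figure for study 1 to reproduce. Its sample size (8565 × 0.03 = 257 MRSA acquisitions, as stated) does not bear on this point. The check is what the schedule produces when antibiotics do nothing.

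**1. The window alone, by hand.** Take the plan's 5% ESBL proportion as a 30-day risk (an assumption): hazard λ = 0.05/30 = 0.00167 per day. Assume perfect swabs, permanent carriage, all outpatient swabs obtained, the same hazard after discharge, and discharge 7 days after the start.
- Untreated, discharge swab only: 1 − exp(−7λ) = 0.0116.
- Treated, last swab on day 30: 1 − exp(−30λ) = 0.0488.
- Ratio 0.0488/0.0116 = 4.2, with no drug effect.

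If no acquisition occurs after discharge, the ratio in this idealised case is exactly 1.0.

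**2. Simulation with the t0 rule applied.** Hazard 0.004 per day in hospital in both groups; antibiotic start on day 2; same stay in both groups. Untreated patients have a discharge swab. Treated patients have swabs at t0, at 3, 7, 15 and 30 days after t0, and at discharge; t0-positives are removed. Assumed ranges: stay 7–15 days, sensitivity 70–90%, post-discharge hazard 0–100% of the in-hospital hazard, 30–80% of outpatient swabs obtained, carriage permanent or lost at 1/30 per day. Treated/untreated ratio of detected acquisition (null value 1.0; values differ slightly between independent runs):

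| Stay | Sensitivity | Post-discharge hazard | Attendance | Ratio |
|---|---|---|---|---|
| 7 d | 0.7 | 50% | 50% | 2.2 |
| 10 d | 0.9 | 50% | 50% | 1.5 |
| 15 d | 0.9 | 50% | 50% | 1.25 |
| 7 d | 0.7 | 100% | 80% | 4.4 |
| 7 d | 0.9 | 0% | any | 0.8 |

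Counting only swabs up to discharge, the ratio is about 0.8–1.3. Most of the inflation therefore comes from the post-discharge window.

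**3. Simulation with both groups starting negative.** This removes the effect of the t0 rule. Hazard as in step 1, stay 7–20 days, sensitivity 0.6–1.0, carriage permanent or lasting 30 or 10 days on average, all outpatient swabs obtained. The ratio runs from 1.0 to 5.4 and is never below 1. Values below 1 in step 2 thus come from removing t0-positives, a rule that acts on treated patients only.

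**4. Candidate repairs under the null.** Settings as in step 2, with the discharge swab as the only outcome in both groups:
- t0-positives kept: 0.99–1.02.
- t0-positives removed: about 0.74–0.95.
- t0-positives counted as untreated acquisitions (equal group sizes assumed): about 0.57–0.81.

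By hand, for stay 7 d, sensitivity 0.9 and permanent carriage:
- Untreated detected: 0.9 × (1 − exp(−0.028)) = 0.0249.
- t0-positive: 0.9 × (1 − exp(−0.008)) = 0.0072.
- Treated after removal: 0.9 × (0.0276 − 0.0072)/(1 − 0.0072) = 0.0185.
- Removal gives 0.0185/0.0249 = 0.74 to 0.75.
- Reassignment gives 0.0185 / [(0.0249 + 0.0072)/1.0072] = 0.58.

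Both make antibiotics look protective when they have no effect.

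**The case against.** **A reader might infer that the swab schedule makes study 1 show an antibiotic effect by construction.** The documents do not support that. Under plausible assumptions the ratio can fall to 0.8, and it is exactly 1.0 if swabs are perfect, carriage is permanent, both groups start negative and nothing acquired after discharge counts. The schedule biases the comparison, usually upward; it does not fix the answer.

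**What does fix the answer is a separate defect.** If cases come from the cohort of antibiotic starters, every case is exposed and every control unexposed, and the odds ratio for antibiotic use cannot be estimated however patients are swabbed. The ratios above describe a treated-versus-untreated contrast of detected acquisition, not the odds ratio of study 1 as written. This stands. It means that unequal swabbing is a second problem, which would remain after case selection was corrected.

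**A reader might also infer that the untreated patients are known to have no follow-up swabs.** The article sets no explicit schedule for study 1 controls, its workflow figure is not available here, and a condensed article may leave control sampling to the full protocol. What can be said is that the article supports at most admission and discharge swabs for them, and that its control definition and matching require no more.

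**Nor is the main result at stake.** The primary outcome is a rate per 1,000 antibiotic-days among treated patients, and case control study 2 compares treated patients who share one schedule.

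**Conclusion.** The concern holds for case control study 1: detection of acquisition depends on antibiotic exposure, and the stated matching does not correct it. With no true effect, the detected ratio is about 1.25–2.2 in middle scenarios (half the in-hospital hazard after discharge, half the outpatient swabs obtained) and 0.8–4.4 over the full assumed ranges. The usual direction is upward, mainly through the post-discharge window.

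The existence of the bias follows from the schedule and the control definition. Its size rests wholly on assumed stay, swab sensitivity, outpatient attendance, carriage duration and post-discharge hazard, none of which the documents give. It adds to the all-exposed cases and all-unexposed controls. The plan should be changed, but this is a flaw in one nested analysis and not in the study's primary outcome.

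**What to change.** For case control study 1 only:
- Define acquisition as negative at admission and positive at the discharge swab, identically for treated and untreated patients.
- Draw cases and controls from both treated and untreated patients. Without this, a common outcome definition does not make the antibiotic effect estimable.
- Do not use day 3–30 or post-discharge positives to make cases.
- Do not apply the exclusion of t0-positives, and do not reassign them to the untreated group. Keep them with their discharge result and state that this dilutes a true effect towards the null, or else handle pre-antibiotic days as unexposed time.
- Use one number for this study in the abstract and the Statistical analysis section.

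Keep the full t0–t4 schedule for the longitudinal analysis and case control study 2.

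**Cost.** No swabs are needed beyond those the abstract lists, provided that the discharge swab really is taken in untreated patients and in t0-positive patients, whom the current text drops from follow-up cultures. This must be confirmed. Untreated patients who acquire carriage must also be identified as possible cases, so the change is more than wording. Study 1 loses cases found only after discharge, or found in hospital but negative at discharge. Those cases stay in the longitudinal analysis and study 2.

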**Discussion:**

The rationale of this study is to better understand the impact of antibiotic use on acquisition, selection and transmission of antimicrobial resistant-bacteria in European hospitals.

**Trial registration:**

ClinicalTrials.gov NCT01208519.

## Background

Despite many efforts, the control of nosocomial antibiotic-resistant infections is still a permanent and unresolved issue in healthcare institutions worldwide facing increased morbidity, mortality and hospital costs [1-3]. Selective pressure exerted by antibiotics plays a central role on the acquisition, selection, persistence and transmission of resistant pathogens which may include the following effects: (1) eradication of the susceptible skin and gut flora will increase the likelihood of acquisition of antibiotic-resistant organisms, especially in settings with endemic resistance; (2) antibiotics select for pre-existing antibiotic-resistant bacteria (ARB) in carriers and enhance the likelihood of spread; (3) antibiotic selection pressure may transform low-level carriers to high-level spreaders; (4) antibiotics active against antibiotic-susceptible bacteria may convert carriers of susceptible bacteria to non-carriers, indirectly promoting acquisition and spread of ARB; (5) antibiotic exposure may increase the risk of endogenous infection with ARB related to changes in colonisation resistance and bacterial virulence at the individual host level [4]. Numerous papers demonstrated that prior antimicrobial drug exposure is a strong risk factor for colonisation and infection due to a drug resistant pathogen [5,6]. A meta-analysis that included 76 studies for a total of 24,230 patients documented that the risk of acquiring methicillin-resistant *Staphylococcus aureus *(MRSA) was increased by 1.8-fold in patients who had taken antibiotics. Antibiotic exposure was determined in the 126 days preceding MRSA isolation [7]. Such risk was almost 3-fold greater after using quinolones or glycopeptides and 2-fold for cephalosporins. A multicentre prospective cohort study conducted in several Italian hospitals showed that 5% of patients were newly colonised by ARB including MRSA in nasal samples, after starting antibiotic therapy. Nine percent of those patients developed an infection by the same strain over the 30-day follow-up. The use of carbapenems was associated with the highest incidence of colonisation with eight new cases of MRSA colonisation for 1,000 antibiotic-day [4].

The likelihood of acquisition of nosocomial ARB during or shortly after therapy with different antibiotic agents is still unclear and is often confounded by scarce data on antibiotic usage at the individual patient level. Study design, selection bias, definition of control groups and failure to control for confounding variables might account for conflicting results [8]. No prospective multi-centre cohort study has been conducted defining, in countries with varying baseline antimicrobial resistance rates, the impact of antibiotic exposure on the development and acquisition of nosocomial carriage by ARB, after accounting for individual and group-level confounding variables, such as case-mix and colonisation pressure [8-10].

## Presentation of the hypothesis

We designed a 2-year observational cohort study (WorkPackage 4 of the EU-funded SATURN project) in order to clarify and determine the role of antibiotic therapy in the acquisition of ARB in hospitalized patients. The study will run in three European hospitals, ranging from 700 to 3,500-bed capacity: Università Cattolica Sacro Cuore "Policlinico A. Gemelli" (UCSC, Rome, Italy), Institute of Infectious Diseases "Matei Bals" (IDMB, Bucharest, Romania), and Clinical Center of Serbia (CCS, Belgrade, Serbia). Overall, 6 medical and 6 surgical wards will be included. All centers obtained ethical approval from the local institution review board.

## Testing the hypothesis

All adult patients (> 18 years) starting intravenous and/or oral antibiotic treatments during hospitalisation will be included in the study. Written informed consent will be obtained by every patient before study inclusion. Exclusion criteria will be pregnancy and recent nose surgery. Patients starting antibiotic therapy *per os *and/or intravenously will be sampled at antibiotic start (t_0_, within one hour) and at the following intervals: day 3 (t_1_), 7 (t_2_), 15 (t_3_), 30 (t_4_) (Figure 1). Patients colonised with MRSA and/or extended-spectrum β-lactamase (ESBL)-producing gram-negative bacteria before starting antibiotic therapy (t_0 _sample) will be excluded from follow-up cultures and analysis. Patients will be followed during the hospitalisation and afterwards for a total of 30-day from the inclusion in the study. Screening will be performed in outpatient clinics after patients' discharge from the hospital, if possible.

**Figure 1 F1:**
[figure not shown]
**Work flow of the SATURN WP4 clinical protocol**.

### Outcomes

The primary outcome will be the rate of acquisition of target antibiotic bacteria by 1,000 antibiotic-days in hospitalised patients. The rate will be also defined according to antibiotic class and single drug. Patients will be stratified by class of risk (e.g., cirrhosis, diabetes, malignancies) and rate of acquisition will be defined. The secondary outcome will be the rate of nosocomial infections by 1,000 days of hospitalisation in newly colonised patients after undergoing antibiotic therapy.

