## Implications of the hypothesis

SATURN project is a European multicentre study that aims to provide an in-depth knowledge of ARB acquisition through the analysis of antibiotic classes, duration of treatment and dosage in the nosocomial setting by a multidisciplinary approach. The SATURN project website http://www.saturn-project.eu provides the information and details concerning the different WPs and the entire project.

Several outcomes will be obtained at the end of the study (December 2014, expected): the rate of acquisition of target ARB by 1,000 antibiotic-days according to different classes of antibiotics, duration of therapy, and antibiotic combinations (monotherapy versus combinations); risk factors associated with new colonisation by target ARB; and risks for nosocomial infections due to target ARB after a cycle of antibiotic therapy adjusted by length of hospitalisation and ward colonisation pressure.

The WP4 study is currently recruiting patients in all clinical centers. The accomplishment of the study will be pursued thanks to the great strive of all clinicians, nurses and microbiology staff in every study step. An advertising campaign (posters, stickers and pictures) was performed in the selected wards in order to thrill and sensitise the recruited staff.

The results of the study should lead to the design of specific infection control measures for preventing spread of ARB in hospitalised non-ICU patients undergoing antibiotic therapy. A potential benefit for selective screening in high-risk patients during antibiotic therapy or shorter duration of antibiotics in such patients might be hypothesised. Readily available colonisation information could impact empiric therapy for nosocomial infections or, for example, the potential need of mupirocin prophylaxis for patients colonised by MRSA during hospitalisation. Assessment of the usefulness of the recommendations derived from the results of the SATURN study should be of valuable help for those in charge of infection control, for hospital administrators, and for those managing budgets of large healthcare organisations.

We do expect that SATURN project results will have a direct impact on clinical practice, improving the appropriateness of antibiotic prescribing policy, the prevention of antibiotic-resistant infections and the heightener of patients' quality care.

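### The class- and drug-specific acquisition rates are defined without stratification or adjustment for hospital, so drug comparisons based on them can be confounded by hospital

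*Protocol article*

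**What the plan says.** All references are to the protocol article.

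- **Primary outcome (Outcomes):** "The primary outcome will be the rate of acquisition of target antibiotic bacteria by 1,000 antibiotic-days in hospitalised patients". The next sentence adds "The rate will be also defined according to antibiotic class and single drug". The one stratification named is by disease: "Patients will be stratified by class of risk (e.g., cirrhosis, diabetes, malignancies) and rate of acquisition will be defined".
- **Formula (Statistical analysis):** "The incidence of colonisation will be defined by the number of new cases of colonisation for 1,000 days of antibiotic therapy".
- **Planned output (Implications of the hypothesis):** "the rate of acquisition of target ARB by 1,000 antibiotic-days according to different classes of antibiotics, duration of therapy, and antibiotic combinations". Monotherapy is to be set against combinations. Adjustment for length of stay and ward colonisation pressure is attached to the nosocomial infection risk, which is a separate item in that list.
- **Setting (Presentation of the hypothesis):** "The study will run in three European hospitals, ranging from 700 to 3,500-bed capacity", one each in Italy, Romania and Serbia, with 6 medical and 6 surgical wards overall.
- **Aim:** The Abstract's primary objective is a comparison of acquisition rates. Background names as the gap to be filled a multicentre study of "in countries with varying baseline antimicrobial resistance rates, the impact of antibiotic exposure on the development and acquisition of nosocomial carriage by ARB", with individual and group-level confounders accounted for.
- **Other analyses (Statistical analysis):** Colonisation pressure is calculated per centre. Kaplan-Meier and Cox analyses are planned with no covariates named. Case control study 2 examines specific antibiotics by multivariable logistic regression. Case control study 1 takes its controls from the same ward, but those controls received no antibiotics. (The Abstract lists the two studies in the opposite order; the numbering here follows Statistical analysis.)

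**The concern.** A rate per drug, formed as events over antibiotic-days with no reference to hospital, is a weighted average of that drug's hospital-specific rates. The weights are the proportions of its antibiotic-days that fall in each hospital. Two drugs used in different proportions across the hospitals are therefore averaged with different weights. If background acquisition also differs between hospitals, the two rates differ even when the drugs act identically everywhere.

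The study chose its sites "in countries with varying baseline antimicrobial resistance rates", so one of the two conditions for this bias is close to a premise of the design. The class and drug rates are a named part of the primary outcome, and the project expects its results to influence prescribing policy. A drug used mainly where acquisition is high could look harmful, and one used mainly where it is low could look safe.

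**Working it through.** **The plan's own figures.** The enrolment target reproduces: 257 MRSA acquisitions / 0.03 = 8,567, against the stated 8,565. The centre targets add up: 48 + 121 + 88 = 257 for MRSA and 95 + 201 + 147 = 443 for ESBL. None of this yields a hospital-specific rate, because no enrolment or antibiotic-days per hospital are given. Dividing each centre's MRSA target by the common 3% would presume equal acquisition everywhere, which is the very thing in question. The illustration below therefore uses no centre sizes.

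**Does any other planned analysis bring hospital in?**

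| Analysis | Compares drugs? | Hospital or ward named? |
|---|---|---|
| Primary rate by class and drug | Yes | No |
| Cox model | Not specified | No |
| Case control study 1 | No (controls have no antibiotics) | Same ward |
| Case control study 2 | Yes | No matching or covariate named |
| Colonisation pressure | No | Calculated per centre, not linked to the rates |

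The Variables section lists ward transfers and room sharing with a carrier, but not hospital, ward or colonisation pressure.

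**Size of the possible bias (assumed inputs).** Let drugs A and B have the same rate as each other within each hospital. Let the three hospital rates stand in the ratio 1 : √R : R. Let a₁, a₂, a₃ be the proportions of drug A's antibiotic-days in the three hospitals, and b₁, b₂, b₃ those of drug B.

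Crude ratio B/A = (b₁·1 + b₂·√R + b₃·R) / (a₁·1 + a₂·√R + a₃·R)

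Example with R = 2, A = 50/30/20% and B = 20/30/50%:

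- A: 0.5 + 0.3 × 1.414 + 0.2 × 2 = 1.324
- B: 0.2 + 0.3 × 1.414 + 0.5 × 2 = 1.624
- Ratio: 1.624 / 1.324 = 1.23

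| R | Mild: 40/35/25 v 25/35/40 | Moderate: 50/30/20 v 20/30/50 | Strong: 70/20/10 v 10/20/70 |
|---|---|---|---|
| 1 | 1.00 | 1.00 | 1.00 |
| 1.5 | 1.06 | 1.13 | 1.27 |
| 2 | 1.11 | 1.23 | 1.51 |
| 3 | 1.17 | 1.37 | 1.89 |
| 4 | 1.21 | 1.47 | 2.20 |

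The hospital-stratified ratio is 1.00 in every cell, since the drugs are equal within each hospital. Swapping A and B inverts the ratios, so the bias can go either way. It vanishes if R = 1 or if both drugs have the same distribution over hospitals.

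**Scale.** Background cites a meta-analysis with almost 3-fold MRSA risk after quinolones or glycopeptides and 2-fold after cephalosporins. That is a between-class contrast of about 3/2 = 1.5. The larger illustrative distortions reach that size; the mild ones do not.

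**How finely can one stratify?** The centre strata would hold 48, 121 and 88 MRSA events. Centre by medical/surgical type gives on average 257/6 ≈ 43 per stratum. All 12 wards give 257/12 ≈ 21, before any split by drug, which is too thin for single drugs.

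**The case against.** The strongest reply is that this treats silence as a decision. The article defines an incidence measure, and it nowhere says that rates will be pooled regardless of centre. Tabulation by centre and covariate lists are commonly left to an analysis plan or full protocol, and neither is shown. The drug question also has its own multivariable analysis, Case control study 2, in which known risk factors are candidates for the model. Colonisation pressure, a confounder that Background names, is at least calculated.

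Much of this stands. A reader might infer that the plan commits to pooling over hospitals and to ranking drugs on the result. The text supports neither: no ranking is announced, and the comparison in the Abstract is not spelled out as drug against drug. Nor can one infer that drug-specific risk will be studied only by unadjusted rates.

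What does not fall away is the definition of the primary outcome, which is protocol content. The article fixes the formula, chooses the breakdowns and names one stratifier, which is not hospital. The analyses that could compensate are not tied to these rates, and none that compares drugs names centre. That does not carry out the aim stated in Background.

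**Conclusion.** The point holds as a weakness in how the primary class and drug rates are specified. Read as written, comparisons based on them do not separate drug from hospital, although the study's rationale calls for this and the data needed are at hand.

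Its actual size and direction cannot be determined. Bias requires both acquisition rates and drug mix to differ between hospitals. The article says only that baseline resistance varies between countries, and gives neither hospital acquisition rates nor drug use by hospital. The range of 1.06 to 2.20 rests entirely on assumed rates and shares; it shows what could happen and is not an estimate. A reader might conclude that the drug results will be seriously biased, but the document does not support that. The matter should be settled in wording before analysis.

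**What to change.** In Outcomes and Statistical analysis:

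1. Keep the crude rates, overall and by class and drug, as description, and show them by centre.
2. State that any comparison of classes, single drugs, or monotherapy with combinations rests on a rate ratio stratified by centre. This can be Mantel-Haenszel, or Poisson regression with antibiotic-days as offset and centre as a factor. Add medical/surgical ward type within centre where events allow; do not stratify by all 12 wards.
3. Stratify the Cox model by centre.
4. Include centre in the logistic model of Case control study 2.

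This changes analysis wording only. Centre is known for every patient, since recruitment targets are set by centre, and ward must be known for the same-ward control selection. The price is wider intervals for drugs used mainly in one centre, because they offer little within-centre contrast. Stratifying by centre removes confounding between hospitals; differences between patients within a hospital still need the planned covariates.
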